### Interim analyses {21b}

Not applicable. Interim analyses will not be performed in the present study.

### Methods for additional analyses (e.g., subgroup analyses) {20b}

Not applicable. Additional analyses are not planned in the present study.

### Methods in analysis to handle protocol non-adherence and any statistical methods to handle missing data {20c}

Per-protocol and intention-to-treat analysis will be performed in order to account for the possible dropouts during the study. In the per-protocol analysis, we will include only the participants who attended at least 85% of the sessions and underwent the baseline and post intervention outcome assessments. For the intention-to-treat analysis, we will consider all the participants who underwent the baseline assessments and after being assigned to one of the study groups took part in at least one session. Missing data will be handled by multiple imputation method. Five imputed data sets will be obtained by multiple linear regression models for each variable. The final imputed value will be the arithmetic mean of the 5 data values created.

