### Intervention description {11a}

Participants allocated to the MICT and HIIT groups will perform two weekly sessions of supervised exercise for 16 weeks. Sessions will be divided into a 3-week adaptation period and 13 weeks of formal training. All sessions will consist of:
Joint mobility (3 min): head and neck, shoulder, elbow, wrist, hip, knee, ankle, and trunk.Warm-up (7 min): treadmill walking at 1–2 km/h.Aerobic component:
MICT group: 15 min on a cycle ergometer at moderate intensity (40–60% of heart rate reserve) or at a perceived exertion rating of 5–6 out of 10.HIIT group: 8 min on a cycle ergometer, including a 60-s sprint at 90% maximal heart rate followed by a 60-s rest until four sets are completed.Strength training: 15 min of exercise in the large muscle groups with weight machines or dumbbells, including 1–2 sets of 8–10 repetitions at 50–60% of one-repetition maximum strength (1RM).Cool-down (5 min): proprioceptive neuromuscular facilitation exercises for abdominal muscles and the pelvic floor will be performed on a mat. Stretching exercises for arm, leg, and trunk muscles will be performed in three 30-s sets. Hemodynamic variables will be checked to ensure that blood pressure and heart rate values return to baseline.

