#### Exercise progression

Beginning with the fourth week, the aerobic load in the MICT group will be adjusted to 60% of the heart rate reserve and the duration will be adjusted to 30 min. In the HIIT group, the number of sets will be increased to 1 by week until 10 sprints. Strengthening exercises will be performed in 3 sets of 10–12 repetitions, with intensities between 60 and 70% 1RM. The 1RM value will be assessed at baseline and week 8.

During both training programs, heart rate, blood pressure, oxygen saturation, and perceived exertion will be evaluated with the Borg CR-10 scale.

Participants allocated to the CG will be following the indications of regular physical activity practice according to WHO (at least 150 min per week of moderate physical activity or at least 75 min of intense physical activity), which will be explained by [name]. The protocol followed by all patients operated of bariatric surgery at the San Juan de Dios hospital is to receive these indications.

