### Criteria for discontinuing or modifying allocated interventions {11b}

Will be criteria for discontinuing: participant request, severe alteration of hemodynamic parameters during the training, participants who attend less than 85% of the training sessions, participants who were absent on evaluation days, and participants from the training group who engage other regular physical exercise.

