### Plans to promote participant retention and complete follow-up {18b}

A weekly phone call will be made to CG participants, asking about their health status and the indications for this group will be reinforced, in turn a text message will be sent to remind the evaluation date and time.

Participants who are in the training groups, in each session will be asked for feedback on their health status and will be sent a text message to remind them the training schedule.

In the event that any participant misses their training or evaluation, they will immediately proceed to call to ask about the reasons for not showing up.

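### The set called intention-to-treat requires at least one attended session, which only the two exercise arms have, so it is a one-sided modified set and not intention-to-treat

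*Protocol article*

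**What the plan says.** Section {20c} of the protocol article defines two analysis sets, each by one rule written for all participants.

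- **Intention-to-treat:** those with a baseline assessment who "after being assigned to one of the study groups took part in at least one session".
- **Per-protocol:** "we will include only the participants who attended at least 85% of the sessions and underwent the baseline and post intervention outcome assessments".

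Sessions belong to two arms. Under Intervention description {11a}, "Participants allocated to the MICT and HIIT groups will perform two weekly sessions of supervised exercise for 16 weeks". For the third arm, Exercise progression says "Participants allocated to the CG will be following the indications of regular physical activity practice according to WHO", and {18b} adds: "A weekly phone call will be made to CG participants, asking about their health status". Neither the advice nor the call is described as a session.

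Elsewhere the word refers to training. The discontinuation criteria in {11b} include "participants who attend less than 85% of the training sessions", and {18b} sets the calls to controls against what happens in the exercise arms: "Participants who are in the training groups, in each session will be asked for feedback on their health status".

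Allocation ({16a} to {16c}) follows the baseline assessment. Only the outcome assessor is blinded ({17a}).

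**The concern.** Attending a first session happens after randomisation, and participants may know their arm by then. Whether someone starts can therefore depend on the arm assigned and on prognosis. Intention-to-treat analysis exists to keep such behaviour from deciding who is counted.

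Controls have nothing to start, so they cannot fail the condition in any meaningful sense. If the rule is applied only where sessions exist, exercise participants who never begin are removed while their counterparts in the control arm stay. The comparison with standard follow-up, an objective in {7}, then sets a selected group against an unselected one under a label that promises otherwise. MICT versus HIIT is less exposed because the condition applies to both arms.

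**Working it through.** **The plan's own figure, for context.** Sample size {14} gives 17 per group for an effect size of 1.01, 5% significance and 80% power. A two-sample t-test with the noncentral t distribution, two-sided (an assumption, since the article does not state sidedness), gives power of 78.9% at 16 per group and 81.5% at 17. The 17 is reproduced and is not in dispute. The 25 per group adds an allowance for dropout.

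**Sessions by arm.** MICT and HIIT: 2 per week × 16 weeks = 32. Controls: none described. The per-protocol threshold is 0.85 × 32 = 27.2, so at least 28 sessions.

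**Two readings of the intention-to-treat rule.**

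1. *Literal.* Controls attend 0 sessions, so 0 of 25 qualify. The set has at most 50 participants, and neither exercise arm can be compared with control. This contradicts {7} and also {20a}, where control is a level of the ANOVA group factor.
2. *Sensible.* The condition applies only where sessions exist. All controls stay, and exercise participants with no session are dropped.

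**Possible size under the second reading.** The following inputs are assumptions that the article does not give:

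- there is no true effect, and the outcome is standard normal in each arm;
- all 25 controls are kept and data are complete;
- a fraction q of an exercise arm never starts, and these are the participants lowest on a trait that correlates r with the outcome.

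The mean of the trait among those kept is φ(z_q)/(1 − q), where z_q is the q-quantile of the standard normal and φ its density. The spurious difference in SD units is r × φ(z_q)/(1 − q).

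- q = 4% (1 of 25): 0.0862/0.96 = 0.090
- q = 10%: 0.1755/0.90 = 0.195

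| Never start | r = 0.2 | r = 0.3 | r = 0.5 |
|---|---|---|---|
| 4% | 0.018 | 0.027 | 0.045 |
| 10% | 0.039 | 0.058 | 0.097 |

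**Scale.** With 25 per arm, the standard error of a difference in means is √(2/25) = 0.283 SD. The largest shift in each row is 0.045/0.283 = 0.16 and 0.097/0.283 = 0.34 standard errors. In simulation, a nominal 5% test rejects about 5.0% to 5.3% of the time with 24 of 25 exercise participants kept. With 22 of 25 kept, it rejects about 5.2% to 6.5% of the time.

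**The case against.** **No analyst would delete the control arm.** A reader might infer that the plan removes all controls. The documents do not support that as an intention: the objectives, the 25 planned controls and the ANOVA group factor all need them. The literal reading shows that the wording is defective, and the second reading is the one to judge.

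**The per-protocol set is selected by design.** A reader might extend the complaint to it, for example by supposing that 32% of exercise participants fall below "participants who attend less than 85% of the training sessions" and deriving a shift of 0.16 to 0.26 SD (0.526 × 0.3 and 0.526 × 0.5). That does not stand. The 32% is 1 − 17/25, an allowance for dropout in every arm, and not a rate of poor attendance. An attendance rule can only apply where there are sessions, the set is labelled per-protocol, and its assessment requirement also removes controls who miss those visits.

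**The direction is not certain.** A reader might infer that the bias must favour exercise. That requires non-starters to have a worse prognosis. It is plausible, but the article gives no data on it. Section {11b} also discontinues training participants who take up other regular exercise; such losses could act the other way.

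**Non-starters may be few.** Participants must be cleared for exercise and consent after participation has been explained, and the trial calls itself an exploratory pilot. This limits the likely size. It does not make the set intention-to-treat.

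**The main analysis is not named.** The article does not say which of the two analyses leads, but an article may leave that to the analysis plan, so it is not part of this point.

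**Conclusion.** The point holds for the intention-to-treat definition. As worded, the rule conflicts with the planned comparison with control. As it would sensibly be applied, it drops randomised non-starters from MICT and HIIT only and should not carry the intention-to-treat label.

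The numerical effect is probably small: 0.018 to 0.045 SD (about 0.02 to 0.05) if 4% never start, and 0.058 to 0.097 SD (about 0.06 to 0.10) if 10% never start with correlations of 0.3 to 0.5. The non-start rates, the correlations and the assumption that non-starters would have done worse are illustrative; none comes from the article. The case for change rests on the definition being wrong and easily put right, rather than on a large demonstrated bias.

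**What to change.** In {20c}:

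- Define the intention-to-treat set as every randomised participant, analysed in the arm assigned, regardless of sessions attended. Handle missing outcomes by the multiple imputation already planned there. How the imputed values are combined is a separate matter.
- In the per-protocol set, apply the 85% criterion to MICT and HIIT only, require the baseline and post-intervention assessments in all three arms, and label the result a supportive, selected comparison.

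Section {11b} must be reconciled with this. It lists attendance below 85% and absence on evaluation days as grounds for discontinuing. The article should make clear that leaving the training does not end outcome assessment, so that outcomes are still collected where possible.

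The cost in {20c} is a few sentences. Baseline precedes randomisation, so every randomised participant should already have baseline data. The real cost is follow-up: redefining the set does not by itself supply outcomes for people who stop training, and the evaluation visits have to be offered to them. The gain is a set that keeps all 75 participants as randomised. With complete data, 25 versus 25 would have 93.8% power at the planned effect size of 1.01.

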### Sample size {14}

GPower 3.1 was used to determine the sample size, assuming a power of 80% and a significance level of 5%. Calculations were based on Herring et al. [37], considering BMI and heart rate as primaries outcomes. This study compared the effects of MICT versus a control group in patients post bariatric surgery. The higher sample size was obtained for the outcome “heart rate.” A total of 17 participants per group were required to detect a significant decrease in the heart rate (effect size = 1.01). However, due to possible dropouts, 25 participants will be included in each group, totaling 75 volunteers.

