## Statistical methods

### Statistical methods for primary and secondary outcomes {20a}

Data normality will be assessed with the Shapiro-Wilk test. Variance homogeneity and sphericity will be assessed with the Levene and Mauchly tests, respectively. For the primary and secondary outcomes that meet the assumptions for the analysis of variance (ANOVA), a mixed model ANOVA with Bonferroni correction will be used to assess the interaction between group (control group vs MICT vs HIIT) and time (baseline vs post 8-week intervention vs post 16-week intervention). Otherwise, data will be analyzed with the Wilcoxon test for within-group comparisons and the Mann-Whitney test for between-group comparisons using the Bonferroni’s correction. The significance level will be set at 5%. Cohen’s *d* will be calculated to determine the effect size. All analysis will be performed in SPSS 24.

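### Averaging the five imputed values into one data set is not valid multiple imputation: the intention-to-treat result is either too precise or pulled to the null, depending on an imputation model that is not stated

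*Protocol article*

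**What the plan says.** Section {20c} of the Protocol article plans a per-protocol and an intention-to-treat analysis. The second set is limited to people assessed at baseline and allocated to a group who attended one session or more. The section then fixes the handling of missing data in three steps:

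- It names the method: "Missing data will be handled by multiple imputation method".
- It makes five completed data sets, with a linear regression for each outcome to be filled in.
- It then combines them cell by cell: "The final imputed value will be the arithmetic mean of the 5 data values created".

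The predictors in those regression models are not listed, and group is not mentioned.

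Section {20a} gives the analysis that follows: "a mixed model ANOVA with Bonferroni correction will be used to assess the interaction between group (control group vs MICT vs HIIT) and time". If the assumptions fail, Wilcoxon and Mann-Whitney tests are used instead. Significance is judged at 5%, and Cohen's d is reported. Nothing there combines results across imputed data sets.

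The sample size section {14} finds 17 participants per group necessary, and "due to possible dropouts, 25 participants will be included in each group".

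**The concern.** Multiple imputation works because each completed data set is analysed on its own and the spread between the five answers is added to the standard error. Averaging the five draws for each missing cell leaves one completed data set, and three things are lost:

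- The between-imputation variance disappears.
- Each filled-in value keeps only about one fifth of its residual variance, so it sits close to the regression line.
- The ANOVA counts imputed participants as observed in its degrees of freedom.

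The difference in means is the same whether one averages first or pools afterwards, because a mean is linear in the data. The damage from averaging is to the standard error, the standard deviation and the p-value.

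The intention-to-treat analysis is the one the plan introduces to deal with dropout, so the defect sits where the missing data are.

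**Working it through.** **The plan's own figure.** With d = 1.01, 80% power and two-sided 5% (sidedness is not stated, so this is assumed), the noncentral t calculation gives 17 per group with power 81.5%. The normal approximation gives 2 × (1.960 + 0.842)² / 1.01² = 15.4, that is 16. The stated 17 reproduces and is not in dispute. The enrolment margin is 1 − 17/25 = 32%. No missing-data rate is given, so 8%, 20% and 32% (2, 5 and 8 of 25 per group) are used as an assumed range.

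**By hand, at 32% missing, baseline correlation 0.5, group in the imputation model.** Take a unit SD at each visit.

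- The true variance of change is 2 × (1 − 0.5) = 1.
- A change built from an averaged imputation, predicted from baseline, has variance of about (1 − 0.5)² + (1 − 0.5²)/5 = 0.25 + 0.15 = 0.40.
- The completed-data variance is about 0.68 × 1 + 0.32 × 0.40 = 0.808, so the SD is √0.808 = 0.90 of the truth.
- The reported standard error of a pairwise difference is about 0.90 × √(2/25) = 0.254.

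Had nobody dropped out, the standard error would be √(2/25) = 0.283. The averaged analysis therefore claims more precision than complete data would give. With only the 17 observed per arm it would be √(2/17) = 0.343.

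**By simulation under the null.** Three groups of 25, three visits, values missing completely at random at 16 weeks (about half of those also at 8 weeks), Bayesian linear regression imputation with five draws, 3,000 runs per setting. The pairwise test is an uncorrected t-test on change from baseline to 16 weeks. The interaction test is the group-by-time ANOVA, assuming sphericity.

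Group in the imputation model:

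| Missing | Correlation | Pairwise, averaged | Pairwise, Rubin | Interaction, averaged | Reported SE / actual SD |
|---|---|---|---|---|---|
| 8% | 0.5 | 6.7% | 5.1% | 7.5% | 0.93 |
| 20% | 0.5 | 9.3% | 4.7% | 11.8% | 0.84 |
| 32% | 0.5 | 13.9% | 4.1% | 21.3% | 0.76 |
| 8% | 0.8 | 6.3% | 4.4% | 6.7% | 0.95 |
| 20% | 0.8 | 11.0% | 4.9% | 14.0% | 0.82 |
| 32% | 0.8 | 14.9% | 4.3% | 22.6% | 0.74 |

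With complete data the interaction test rejects 4.6% to 5.8% of the time. At 32% and correlation 0.5 the averaged analysis reports a standard error of 0.254 against an actual sampling SD of 0.334; Rubin's rules give 0.338. Pairwise simulations at other settings gave about 7% to 9.5% at 16% missing and about 14% to 16% at 32%.

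Group left out of the imputation model: the averaged pairwise test rejects 5.0% to 5.5% of the time and the interaction test 5.1% to 5.4%. But imputed participants then carry no group difference, so the effect shrinks by roughly the observed share: 0.60 × 0.68 = 0.41. Simulation at 32% missing and correlation 0.5 gives 0.40 for a true 0.60 SD.

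**Cohen's d.** For a true difference of 0.60 SD at 32% missing, group in the model gives d = 0.69 against 0.61 on full data (correlation 0.5) and 1.10 against 0.96 (correlation 0.8). Without group it is 0.44 against 0.60 and 0.71 against 0.97. At 8% missing with group in the model the inflation is about 2–3%.

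**The case against.** The strongest reply is that the harm is conditional and may be small. Most of this stands.

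- A reader might infer that the 5% test fails and Cohen's d is inflated whatever is done. The document does not support that. It lists no imputation predictors, and without group the error rate holds near 5% and d is too low. That attenuation comes from omitting group, not from averaging.
- A reader might take 32% as the expected missing rate. The plan states only an allowance for dropouts. Participants who never attend are outside the intention-to-treat set and are not imputed, and the discontinuation criteria in {11b} include low attendance and other regular exercise, neither of which implies a missing outcome. The imputed share could be well below 32%, and at 8% the inflation is modest.
- A reader might describe the affected analysis as fully preserving randomisation. Because it requires at least one session, it does so only approximately.
- The pairwise figures are for an uncorrected t-test, whereas {20a} plans an interaction test with Bonferroni correction. The simulated interaction figures are larger, but carry the same condition on group.
- The trial is an exploratory pilot, the intention-to-treat analysis is not named as primary, and the per-protocol analysis requires baseline and post-intervention assessments, so it is largely untouched.

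What does not stand is that a separate analysis plan could simply fill in the detail. The averaging rule is explicit, so such a plan would have to reverse it. Nor does the pilot label remove the point: the plan tests directional hypotheses at 5%, and the Discussion presents confirmation as a possible starting point for recommendations.

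**Conclusion.** The concern holds in conditional form. Averaging the draws and analysing one data set is wrong as stated, under either reading of the imputation model. If group is included, standard errors at 32% missing are about three quarters of what they should be, and false positives exceed 5% by an amount that grows with missingness, from slight at 8% to roughly threefold at 32% for a pairwise test. If group is omitted, the error rate is kept, but only because the estimate and its variability shrink together, and a real effect is understated by about a third at 32% missing.

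The sizes rest on data missing completely at random, normal outcomes, visit correlations of 0.5 to 0.8 and a missing share that the document does not give. The direction in each case does not depend on the exact share.

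**What to change.** Delete the averaging sentence in {20c} and choose one of two routes.

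1. Keep multiple imputation. Put group, baseline and all visits in the imputation model, analyse each completed data set separately, and pool estimates and standard errors by Rubin's rules. More than five imputations is desirable but not essential: five, properly pooled, gave 4.1% to 5.1% in the table above. Naming group is part of the fix, because pooling alone leaves the estimate at 0.40 for a true 0.60 SD if group is omitted.
2. Fit a likelihood-based repeated-measures mixed model to all observed visits, without imputing the outcome.

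The rank-test fallback in {20a} needs its own sentence, since those tests give no estimate and standard error to pool: apply them to observed data, or replace them with a method whose estimate can be pooled. Cohen's d should not be computed from averaged imputations.

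The cost is a revised paragraph in {20c}, that added sentence in {20a}, and slightly more analysis work. Intervals become wider and honest. Design, visits and sample size do not change.

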### Plans to give access to the full protocol, participant level-data and statistical code {31c}

Not applicable. Public access to the full protocol, data sets, and statistical code are not planned for this trial. However, this information might be available upon a reasonable request to the corresponding author keeping participants’ anonymity.

## Oversight and monitoring

### Composition of the coordinating center and trial steering committee {5d}

The center is coordinated by [name] and the leading researcher [name]. The trial will be directed by the principal investigators [name] and [name]. No additional steering committee is considered for this study. All researchers will meet weekly to discuss the research progress and possible unforeseen events.

